### Outcomes

The primary outcome measure is the percentage of people that remains under good cardiometabolic control, defined as having HbA1c ≤7.5% and systolic blood pressure ≤145 mmHg and total cholesterol ≤5.2 mmol/l. Secondary outcome measures are HbA1c, blood pressure, cholesterol, Body Mass Index, fasting blood glucose, smoking behaviour, physical activity, loss of work due to illness, health status, diabetes-specific distress, satisfaction with treatment and adherence to medications. These outcomes are collected either from the medical records or from a patient questionnaire.

#### Medical records

Biomarkers (HbA1c, cholesterol, fasting blood glucose) and anthropometric variables (blood pressure, Body Mass Index) will be collected from the general practitioners' computerised information system. Information on the most recently measurements of the biomarkers and anthropometric variables before the study, medical history, medication use before the study and all measurements performed during the first EFFIMODI visit will be collected just after the start of the study. All measurements during the follow-up period will be collected after the end of the follow-up period. The same applies to the number of diabetes and non-diabetes related visits to the general practitioner and (differences in) medication use during the study.

#### Questionnaires

The participants will be asked to complete an extensive questionnaire before (t = 0) and after (t = 18 months) the intervention period. This questionnaire comprises general background information on age, gender, ethnicity, education, smoking, physical activity, occupation and loss of work due to illness, health status, diabetes-specific distress and satisfaction with diabetes treatment.

Current smoking is measured as the number of cigarettes per day or the number of cigars per week. Smoking in the past is measured the same way. Also the number of pack years is recorded. Physical activity is measured with the Short Questionnaire to Assess Health-enhancing physical activity (SQUASH) [10]. The SQUASH is a reliable and valid questionnaire to measure the level of physical activity in an adult population. The questionnaire was designed to give an indication of the habitual activity level. Information on light (range: 2-4 Metabolic Equivalent of Task (MET)), moderate (range: 4-6.5 MET) and vigorous (>6.5 MET) intensity physical activities will be obtained. Physical activity will be expressed in minutes per week and in a total activity score. The total activity score will be calculated by multiplying the minutes per week by the actual MET score of the specific activity (MET/min/week).

Occupation and loss of work due to illness are measured with the Short Form Health and Labour Questionnaire (SF-HLQ) [11]. The SF-HLQ consists of three parts: absenteeism from paid work, production losses without absenteeism from paid work and hindrance in the performance of paid and unpaid work. Data derived with this questionnaire will be used to calculate costs of productivity losses, should incremental cost-effectiveness be merited at closure of the trial (see **economic evaluation**).

Two questionnaires are used to measure health status: Short-Form 36 (SF-36) [12] and EQ-5D [13]. The SF-36 generates a profile of scores on eight dimensions of health. These dimensions are: (1) physical functioning; (2) limitations due to physical difficulties (physical role functioning); (3) bodily pain; (4) social functioning; (5) mental health; (6) limitations due to emotional difficulties (emotional role functioning); (7) vitality; and (8) general health perception. For all eight dimensions an average score for all items in the scale is calculated, with a range from 0 (least favourable health state) to 100 (most favourable health state). Two summary scales for mental and physical functioning can be calculated as well. The SF-36 is validated in the Dutch population [14].

The EQ-5D is a generic questionnaire, consisting of a Visual Analogue Scale (EQ-5D VAS) and a classification system (EQ-5D Profile) [13]. The EQ-5D Profile covers five domains of health (mobility, self-care, usual activities, pain/discomfort and anxiety/depression), each with three levels of functioning: level 1, no problems; level 2, some problems; level 3, severe problems. The EQ-5D VAS is a graded, vertical line, anchored at 0 (worst imaginable health state) and 100 (best imaginable health state). The patient is asked to mark a point on the EQ-5D VAS that best reflects his/her actual health state.

To measure diabetes-specific distress, the Problem Areas In Diabetes (PAID) questionnaire is used [15]. This is a widely recognised measure of diabetes distress, assessing the general emotional burden of diabetes and distress related to treatment, food choices and social support. The 20 items are scored on a 5-point scale yielding a sum score (0-80), with higher scores representing higher distress. The Dutch PAID scale has good convergent and discriminate validity and high internal consistency [16].

To measure satisfaction with diabetes treatment, the Diabetes Treatment Satisfaction Questionnaire (DTSQ) is used [17]. The DTSQ measures satisfaction with treatment regimen (six items), perceived frequency of hyperglycaemia (one item) and perceived frequency of hypoglycaemia (one item) over the past few weeks. The treatment satisfaction score can range from 0 (very dissatisfied) to 36 (very satisfied).

#### Economic evaluation

To be able to calculate direct health care costs, data on health care use are needed. Data concerning consultations beyond the planned monitoring consultations, medication use and referral rates to other health care professionals will be collected from the general practitioners' computerised Information System. Should this trial provide evidence that three-monthly monitoring results in better outcomes than six-monthly monitoring, an incremental cost-effectiveness analysis becomes warranted, that quantifies the additional cost related to the additional health effects. For such an economic evaluation we will use data on health care use as recorded in the information system of the general practitioners, and data recorded with the SF-HLQ and the EQ5D (see above). The EQ5D is of special importance, as utilities, and consequently, quality adjusted life years (QALYs) can be elicited using this generic questionnaire.

### Sample size calculation

The sample size is calculated on the assumption of equivalence of cardiometabolic control. Therefore, we used the formula from Jones et al. [8]: n = (2p(100-p)*(Z_(1-α)_+Z_(1-β)_)^2^)/δ^2^, where p is the overall percentage of successes to be expected if the treatments are equivalent, δ indicates the range of equivalence for the difference in percentage success rates, α is the probability of type I error and β the probability of type II error.

We assume equivalence if the two-sided 95% confidence interval (α = 0.05; Z_(1-α) _= 1.96) for the difference in cardiometabolic control between the two intervention groups is completely in the range from -5 to 5% (δ = 5). With a supposed overall percentage of success of 95% and a power of 90% (β = 0.1; Z_(1-β) _= 1.28), we need a sample size of 399 people per randomised group. Based on a small survey that was performed by the Julius Center, we assume that ~50% of the people have no preference and thus will be randomised. About the other half of the people is assumed to have a strong preference for the frequency of monitoring. Therefore, we need to include 1596 patients: 798 in the randomised arms and 798 in the observational arms.

As said earlier in the **study population **section, we assume that 20% of the type 2 diabetes patients will fulfil the inclusion criteria. With an average of 80 type 2 diabetes patients per practice, we expect that sixteen patients in each general practice will meet the eligibility criteria. Taking into account a response rate of 60%, ten patients in each practice will be willing to participate in the study: five in the observational arm and five in the randomised arm, so at least 160 general practitioners will have to be recruited. As people may drop out during the study, we will recruit 1800 patients allowing an 11% drop-out; therefore we need 180 general practitioners. Figure 1 shows the participant flowchart with the expected numbers.

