### Study population

Patients are eligible for the study if they are between 40 and 80 years old, diagnosed with type 2 diabetes for more than a year, treated by their general practitioner, not on insulin treatment and overall well-controlled, defined as having HbA1c ≤7.5% and systolic blood pressure ≤145 mmHg and total cholesterol ≤5.2 mmol/l. These HbA1c, systolic blood pressure and total cholesterol values are a little higher than the Dutch target values (HbA1c ≤7.0%, systolic blood pressure ≤140 mmHg and total cholesterol ≤4.5 mmol/l [3]). We decided to choose more liberal values to create a larger target population to be randomised. According to the stricter target values only 18.9% of all type 2 diabetes patients fulfilled these values [9]. Because of the minimal difference with the target values, we assume that 20% of the type 2 diabetes patients will fulfil the inclusion criteria.

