### Recruitment of practices and patients

We will approach the boards of several health care groups to recruit general practitioners. These health care groups have a central database in which all type 2 diabetes patients are recorded. In this database all determinants that are needed for the selection of study patients are included (see **study population **for the inclusion criteria). The health care groups will ask all their affiliated general practitioners to participate in the study. If a general practitioner wants to participate he will obtain the selection of patients, according to the inclusion criteria, from the health care group. The general practitioner sends an information letter as well as an informed consent form to the selected patients.

Patients who want to participate have to fill in the informed consent form. The participants are asked whether they strongly prefer three-monthly (current care) or six-monthly diabetes control or whether they have no preference. Patients with a preference will enter the 'observational arm'. If participants do not have a strong preference for the frequency of care, they will be randomised.

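### The stated 90% power depends on a 95% success rate that is probably too high; under the plan's ±5-point rule, power with 399 per arm is about 80% at 95% success and 31% at 90%

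*Protocol article*

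**What the plan says.** All references are to the protocol article.

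- **Entry (Study population).** A patient must have HbA1c ≤7.5%, systolic blood pressure ≤145 mmHg and total cholesterol ≤5.2 mmol/l, besides the criteria on age, diabetes duration, care setting and insulin. Overall, "we assume that 20% of the type 2 diabetes patients will fulfil the inclusion criteria". The Dutch target values are stricter (7.0%, 140 mmHg, 4.5 mmol/l).
- **Primary outcome (Outcomes).** "The primary outcome measure is the percentage of people that remains under good cardiometabolic control", with good control defined by the same three cut-offs as at entry.
- **Decision rule (Sample size calculation).** "We assume equivalence if the two-sided 95% confidence interval" for the difference between the arms lies "completely in the range from -5 to 5"%.
- **Size (Sample size calculation).** "With a supposed overall percentage of success of 95"% and 90% power, the conclusion is "we need a sample size of 399 people per randomised group". Recruitment is raised to 1800 to allow for 11% drop-out.

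**The concern.** The success rate p sets the variance through p(1-p), so the sample size depends on it directly. Two features of the design point to a rate below 95%.

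First, there is no gap between the entry and outcome cut-offs. Someone who enters just under a cut-off fails if one of three values is slightly higher at follow-up. Second, entry selects on measured values that vary from one occasion to the next. Some of those who pass at selection will be over a cut-off on re-measurement with no real change in control. For scale, if the three components were independent, 95% for the composite would require 0.95^(1/3) = 98.3% for each. Positive dependence between them would lower that figure.

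If p is lower, the confidence interval widens towards the 5-point margin. The trial could then end without a conclusion even if the two schedules are truly equivalent. The Economic evaluation text expects an equivalent result to be enough to change monitoring practice, so an inconclusive result would be costly.

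**Working it through.** **Inputs.** From Sample size calculation: p = 95%, margin δ = 5 points, Z = 1.96 (two-sided 95% interval), Z = 1.28 (90% power), n = 399 per arm, 1800 recruited with about half randomised. From Randomisation and blinding: 1:1 allocation. The true difference is taken as zero, as the plan's formula implies.

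**Step 1: reproduce 399.** n = 2p(100-p)(1.96+1.28)²/δ² = 2×95×5×10.4976/25 = 398.9, so 399. The figure reproduces.

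**Step 2: power of the stated rule at p = 95%.** The rule needs both ends of the interval inside ±5. With zero true difference,

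power = max(0, 2Φ(0.05/SE − 1.96) − 1), where SE = √(2p(1-p)/n).

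At p = 0.95 and n = 399, SE = √(0.095/399) = 0.01543, and 0.05/SE − 1.96 = 1.28. Φ(1.28) = 0.90, so power = 2×0.90 − 1 = 80% (simulation 79%). The 90% is the chance of clearing one limit only. For both limits the formula needs Z(1-β/2) = 1.645, which gives 2×95×5×(1.96+1.645)²/25 ≈ 494 per arm. The fall from 90% to 80% is therefore due to the formula and not to the success rate.

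**Step 3: power at other success rates.** The column for one limit follows the plan's own formula. It separates the effect of p from the effect found in Step 2.

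| p | 95% half-width, n = 399 (points) | One limit, n = 399 | Stated rule, n = 399 | Stated rule, n = 450 | n per arm by the plan's formula |
|---|---|---|---|---|---|
| 95% | 3.02 | 90% | 80% | 86% | 399 |
| 93% | 3.54 | 79% | 58% | 67% | 547 |
| 90% | 4.16 | 65% | 31% | 41% | 756 |
| 85% | 4.95 | 51% | 1% (simulation 4%) | 11% | 1071 |

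The 450 is 1800/2/2, that is, everyone recruited to a randomised arm.

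**Step 4: where the rule stops being attainable.** Set 1.96√(2p(1-p)/n) = 0.05, so p(1-p) = n(0.05/1.96)²/2.

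- n = 399: p(1-p) = 0.1298, so p = 84.7%.
- n = 450: p(1-p) = 0.1464, so p = 82.2%.

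Enumerating all pairs of event counts with 399 per arm confirms that the lowest pooled observed rate that can satisfy the rule is 84.7%. This limit applies to the observed rate. At a true rate of 84%, simulation gives a 1.5% chance of meeting the rule; at 82% the chance is 0.1%.

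**The case against.** **The 20% does not contradict the 95%.** A reader might infer that they clash. They do not: 20% is a cross-sectional share of all type 2 patients meeting every inclusion criterion, and 95% is retention among selected, treated patients. Neither bounds the other, and the article gives no separate figure for the share meeting the three entry cut-offs. This objection stands in full.

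**Retention cannot be calculated from the documents.** One could take 20% as the joint pass rate of three independent, stable normal measures. Retention would then be 49% to 77% for test-retest correlations of 0.7 to 0.95, and a correlation of about 0.998 would be needed for 95%. The documents support neither that calibration nor those correlations, so these figures are not relied on here.

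**Treatment to target provides a buffer.** The Dutch targets are stricter than the outcome cut-offs, and treatment targets stay the same in both arms. A patient drifting upwards passes the target before failing the outcome. This may raise retention, and it tempers the expectation of a lower rate. It does not show that 95% will be reached.

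**The limit is not absolute.** A reader might infer that equivalence can never be concluded when the true rate is below 84.7%. That is too strong, because the limit applies to the observed rate, a Wald interval and 399 analysed per arm. Intention-to-treat with multiple imputation could keep 450 per arm in the analysis, although imputation would not restore full information. Even with 450 complete, power at 90% success is 41%.

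**The source of the 95% may be in the full protocol.** The article is a condensation, so a missing citation is not the point here. The point is that the published power depends steeply on this value, and that the design itself suggests a lower one.

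**Conclusion.** The point holds. The stated 90% power is not delivered under the plan's own rule even at 95% success, where it is about 80%. It falls to about 58% at 93%, 31% at 90% and 1–4% at 85%. These figures assume 399 analysed per arm, no true difference and an unadjusted normal-approximation interval; they need no model of retention.

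That the rate will be below 95% is a reasoned expectation, from identical entry and outcome cut-offs and regression to the mean. How far below cannot be determined from the documents. By the plan's own formula, a five-point error in p raises the required size from 399 to 756 per arm, so the assumption needs support before the trial relies on it.

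**What to change.** Before enrolment, check whether the health care groups' central database holds earlier values. The Recruitment section says of it: "In this database all determinants that are needed for the selection of study patients are included", but does not say that it keeps histories. If it does, compute the share of patients meeting the entry criteria who still meet all three cut-offs about 18 months later. Then:

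1. Replace the 95% with that estimate or, if no history is available, with a justified range.
2. Restate the power of the ±5-point rule for 399 per arm over that range, requiring both limits to be met. At 95% this is about 80%.
3. State the success rate below which the rule cannot be met: an observed rate of about 84.7% with 399 analysed per arm, or 82.2% with 450.

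The cost is one query on a database already used for recruitment, revised wording, and a less favourable stated power.

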### Randomisation and blinding

Participants without a preference for either three-monthly or six-monthly monitoring are randomised into one of the two randomised study arms in a 1:1 ratio: a control group that will receive current care, comprising diabetes control once per three months, and an intervention group that will receive diabetes control once per six months. In both randomised groups the extensive annual check-up will be done by the general practitioner. The treatment targets, therapeutic algorithms and life style advices will remain unchanged and do not differ between the intervention and control groups.

Randomisation is generated at the patient level by a computerised random-number generator at the Julius Center. Participants are randomised before baseline data are collected. Since this is a pragmatic trial, it is not necessary to blind participants and general practitioners for the treatment allocation. However, the laboratory technicians who measure HbA1c and cholesterol are not aware of study participation of the patients.

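### 399 per arm gives about 80% power, not 90%, for the stated two-sided equivalence rule

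*Protocol article*

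**What the plan says.** All the elements are in the Sample size calculation section of the protocol article.

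- **Decision rule:** "We assume equivalence if the two-sided 95% confidence interval (α = 0.05; Z_(1-α) _= 1.96") for the difference in cardiometabolic control "is completely in the range from -5 to 5% (δ = 5"). Both limits must fall inside the margins.
- **Formula:** "n = (2p(100-p)*(Z_(1-α)_+Z_(1-β)_)^2^)/δ^2", where "p is the overall percentage of successes to be expected if the treatments are equivalent". The calculation therefore assumes a true difference of zero.
- **Success rate:** "With a supposed overall percentage of success of 95"%.
- **Result:** "a power of 90% (β = 0.1; Z_(1-β) _= 1.28), we need a sample size of 399 people per randomised group".
- **Drop-out:** "we will recruit 1800 patients allowing an 11% drop-out".

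The Randomisation and blinding section sets the allocation: participants without a preference are "randomised into one of the two randomised study arms in a 1:1 ratio". The Study design section says that an equivalence design was chosen and a non-inferiority design was not.

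**The concern.** An equivalence rule based on a confidence interval is two tests at once: the lower limit must exceed -5 and the upper limit must stay below +5. When the true difference is zero, the two ways of failing are equally likely and practically never occur together, so the total risk of failure is twice the risk at one margin. A formula with Z(1-β) controls the risk at one margin only. To hold the total at β, each side may take only β/2, which calls for Z(1-β/2).

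The printed 90% would then be the power of a one-sided comparison, reported for a two-sided rule. The 399 leads directly to the 798 randomised, the 1596 and 1800 patients in total, and the 160 and 180 general practitioners. The Economic evaluation part of the analysis plan also makes the choice of six-monthly monitoring and the cost-minimisation analysis depend on showing equivalence. An overstated power hides how likely the trial is to end without that answer.

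**Working it through.** **Inputs, all from the Sample size calculation section except the 1:1 ratio (Randomisation and blinding):** p = 95%, δ = 5 points, critical value 1.96, Z(1-β) = 1.28, n = 399 per arm, true difference 0.

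**1. The plan's own figure.**
n = 2 × 95 × 5 × (1.96 + 1.28)² / 5² = 950 × 10.4976 / 25 = 398.9, so 399. The figure reproduces.

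**2. Power of the stated rule at n = 399.**
- SE of the difference = √(2 × 95 × 5 / 399) = √(950 / 399) = 1.543 points.
- Margin in SE units: 5 / 1.543 = 3.240. Less the critical value: 3.240 − 1.96 = 1.280.
- Chance of clearing one margin: Φ(1.280) = 90.0%.
- Chance of clearing both: 2Φ(1.280) − 1 = 2 × 0.900 − 1 = 80.0%.

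**3. Check without the normal approximation.** Exact enumeration over two binomials (399 per arm, 95% in each), both 95% limits required inside ±5:

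| Interval | One margin | Both margins |
|---|---|---|
| Wald | 89.7% | 79.4% |
| Newcombe | 88.1% | 76.2% |

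**4. Size needed for 90% under the same rule.** With Z(1-β/2) = 1.645:
n = 950 × (1.96 + 1.645)² / 25 = 493.8, so 494 per arm, which is 24% more than 399. The normal approximation gives 90.0% power at 494; exact Wald enumeration gives 89.7%.

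**5. Could the 399 come from a 90% interval (two one-sided tests at 5%)?** With 399 per arm such an interval would give 2Φ(3.240 − 1.645) − 1 = 88.9%, close to 90%. But the text fixes a 95% interval and 1.96. Using 1.645 with 1.28 gives about 325, and 1.645 with 1.645 gives about 411. Neither is 399, so that was not the calculation made.

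**6. Does the drop-out allowance close the gap?** Of 1800 recruited, half are expected to be randomised, so 450 per arm. If none were lost, SE = √(950 / 450) = 1.453, 5 / 1.453 − 1.96 = 1.481, and power = 2Φ(1.481) − 1 = 86.1% (85.7% exact, Wald).

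**7. The label on α.** Z(1-α) at α = 0.05 is 1.645. The value used, 1.96, is Z(1-α/2), which is right for a two-sided 95% interval. This is a slip of notation and changes no number.

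**The case against.** The error does not touch the validity of a positive result. The type I error, the estimate and the interval are unaffected; what rises is the chance of an inconclusive trial. The lower margin, which asks whether six-monthly monitoring is worse, does have 90% power at 399, and that is the direction the economic section acts on. This is true and limits the harm. It does not make the stated figure correct, because the rule requires both margins and the Study design section sets non-inferiority aside.

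The 20% risk of failure also applies to 399 analysed patients per arm. With better retention, and with the planned intention-to-treat analysis and multiple imputation, the effective number could lie between 399 and 450, and the risk between about 20% and 14%. That is a fair qualification. But 399 is the number the plan itself relies on after drop-out, imputation does not recover all lost information, and even complete follow-up of 450 falls short of 90%.

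One could also say that the formula is a published one. Whether it is printed as in its source cannot be checked here, and it does not matter: the printed inputs do not give the printed power under the printed rule.

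**Conclusion.** The concern holds. With 399 analysed per arm, the stated equivalence rule has about 80% power, 10 points below the claimed 90%. The 90% is the power for one margin only. For 90% under the same rule, the plan's formula gives 494 per arm, a shortfall of 95 per randomised arm.

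This rests on the plan's own assumptions: 95% success in both arms, a true difference of exactly zero, 1:1 allocation and a 95% interval. Any true difference lowers the power further. With true rates of 95% and 94%, for example, exact enumeration with a Wald interval at 399 per arm gives about 66%.

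**What to change.** **Minimum change, wording only.** State that 399 per arm gives about 80% power for the two-sided 95% interval to lie wholly within ±5 points, at 95% success and no true difference. Label 1.96 as Z(1-α/2) with α = 0.05, or equivalently as a type I error of 2.5% at each margin. The cost is a less favourable stated power.

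**If 90% is to be kept with the same rule.** Replace Z(1-β) by Z(1-β/2) = 1.645 and state 494 per arm. The dependent totals then become:

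- randomised: 2 × 494 = 988, instead of 798;
- all participants, with half having no preference: 2 × 988 = 1976, instead of 1596;
- recruited, with 11% drop-out: 1976 / 0.89 = 2220.2, so 2221, instead of 1800;
- practices, at ten participants each: 223, instead of 180.

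Deciding on the lower margin alone at one-sided 2.5% would also give 90% with 399 per arm. That is not a wording change: it turns the trial into a non-inferiority trial and contradicts the Study design section. It should not be adopted merely to rescue the power figure.

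### The expected yield of 9.6 participants per practice is rounded up to ten, so 180 practices would give 1728 patients rather than 1800 and leave room for about 7.6% drop-out, not 11%

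*Protocol article*

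**What the plan says.** All the figures are in the protocol article, Methods and design, Sample size calculation.

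- Patient target: "we need to include 1596 patients: 798 in the randomised arms and 798 in the observational arms". This is four times the 399 per randomised group, because about half of the participants are expected to have no preference and so to be randomised.
- Eligible share: "we assume that 20% of the type 2 diabetes patients will fulfil the inclusion criteria".
- Practice size and eligible patients: "With an average of 80 type 2 diabetes patients per practice", "we expect that sixteen patients in each general practice will meet the eligibility criteria".
- Participants per practice: "Taking into account a response rate of 60%, ten patients in each practice will be willing to participate in the study", split as five observational and five randomised.
- Practices before drop-out: "so at least 160 general practitioners will have to be recruited".
- Practices with the drop-out allowance: "we will recruit 1800 patients allowing an 11% drop-out; therefore we need 180 general practitioners".

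The section gives ten without a qualifier and offers no reason for it beyond the 60% response rate.

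**The concern.** Sixteen eligible patients at a 60% response rate is 9.6 participants, not ten. Rounding to a whole patient would be harmless in a description of a typical practice. Here the rounded figure is the divisor that sets how many practices are needed, and a yield rounded upwards always understates that number. The printed inputs and the printed practice counts therefore disagree. If every planning assumption came true exactly, the stated number of practices would not deliver the stated number of patients, and part of the reserve meant for drop-out would be used up before anyone dropped out.

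**Working it through.** **Inputs** (all from Sample size calculation): 80 patients per practice; 20% eligible; 60% response; 399 per randomised group; 1596 patients in total; 1800 to be recruited; 11% drop-out; expected success 95%; equivalence range ±5 percentage points; Z values 1.96 and 1.28. As the plan does, one recruited general practitioner is taken as one practice of 80 patients.

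**Reproducing the plan's figures**

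- Per group: 2 x 95 x 5 x (1.96 + 1.28)² / 5² = 398.9, so 399.
- Total: 4 x 399 = 1596.
- Drop-out: 1596 / (1 − 0.11) = 1793.3, so 1794. The plan uses 1800, which implies 1 − 1596/1800 = 11.3% and is consistent with the stated 11%.
- Practices at ten each: 1596/10 = 159.6, so 160; 1800/10 = 180.

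Every printed figure is reproduced, but the two practice counts only with a yield of exactly ten.

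**Yield from the stated inputs**

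- Eligible per practice: 80 x 0.20 = 16.
- Participants per practice: 16 x 0.60 = 9.6.

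**Patients delivered at 9.6 per practice**

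| Practices | Expected patients | Plan's target | Shortfall |
|---|---|---|---|
| 160 | 160 x 9.6 = 1536 | 1596 | 60 (3.8%) |
| 180 | 180 x 9.6 = 1728 | 1800 | 72 (4.0%) |

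**Practices needed at 9.6**

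- For 1596: 1596/9.6 = 166.25, so 167.
- For 1800: 1800/9.6 = 187.5, so 188.

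**Effect on the drop-out reserve**

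- Planned reserve: 1800 − 1596 = 204 patients.
- Reserve at 1728: 1728 − 1596 = 132 patients. The rounding takes 72 of the 204, about 35%.
- Drop-out that can be absorbed before falling below 1596: 132/1728 = 7.6%.

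**Effect on power, if recruitment stopped at 180 practices and 11% dropped out**

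- Remaining: 1728 x 0.89 = 1537.9 patients; divided by 4, about 384 per randomised group.
- Solving the plan's formula for power, with proportions in place of percentages: power = Φ(0.05 / √(2 x 0.95 x 0.05 / n) − 1.96).
- n = 399: Φ(3.240 − 1.96) = 90.0%.
- n = 384.5: Φ(3.181 − 1.96) = 88.9%.

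The loss is about one percentage point.

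**The case against.** The strongest reply is that nothing in the design depends on the practice count. The 399 per group and the 1596 in total come from the formula, and the plan's commitment is in patients: "we will recruit 1800 patients allowing an 11% drop-out". If practices yield slightly fewer than ten, more can be added. The first count is worded as a minimum and is replaced in the next sentence by 180, and 180 practices still give more than 1596 patients before drop-out. All of this stands. The figure of 384 per group arises only if recruitment stops at 180 practices, which the document does not say. It also treats every drop-out as lost information, whereas the Analysis section plans multiple imputation, so it is the unfavourable end.

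The inputs are also rough. A response rate of 62.5% (10/16), an eligible share of 20.8% (10/48) or 83.3 patients per practice (10/0.12) would give ten exactly. That is fair, and it is why the point is small. It does not make the printed figures agree, because the plan states 80, 20%, sixteen and 60%, and these give 9.6.

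Two stronger readings are tempting and should not be drawn.

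- A reader might infer that the rounding adds to a wider overstatement of power. By the plan's own formula it costs about one point, and only on the stopping assumption above. Whether that formula uses the right error term for an equivalence criterion is a separate question, and the rounding has no bearing on it.
- A reader might infer that the recruiting unit is ambiguous, because the yield is counted per practice and the requirement in general practitioners. The wording is loose, but it is consistent if one participating practitioner stands for one list of 80 patients, and no passage contradicts that.

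**Conclusion.** The point holds as a minor arithmetic error in the optimistic direction. On the plan's own inputs the practice counts of 160 and 180 fall about 4% short of the patient numbers they are said to deliver. The practical consequence is that 180 practices would cover about 7.6% drop-out instead of the stated 11%. The required sample size, the equivalence range and the planned analysis are untouched. The result rests on taking the 80, 20% and 60% at face value and on one practice per recruited practitioner; the loss of about one point of power further assumes that recruitment ends at 180 practices and that the full 11% drops out.

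**What to change.** Carry 9.6 through the calculation and correct the statement, in one of two ways.

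- Keep the patient targets and restate the requirement as 167 practices for 1596 patients and 188 for 1800. Check: 167 x 9.6 = 1603 and 188 x 9.6 = 1805. This means eight more practices than the 180 now planned.
- Keep 180 practices and state the expected yield as 1728 patients with a drop-out allowance of about 7.6%. This needs no extra practices, but the text should then no longer say that 180 practices cover 11%.

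Either is an edit to one paragraph, and the practice counts and yields shown in the participant flowchart should be checked against it. No change to the design or the analysis follows.
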